## Abstract

**Background:**

Among adult kidney transplant recipients, non-adherence to immunosuppressive medications is the leading predictor of poor outcomes, including rejection, kidney loss, and death. An alarming one-third of kidney transplant patients experience medication non-adherence even though the problem is preventable. Existing adherence interventions have proven marginally effective for those with acute and chronic illnesses and ineffective for adult kidney transplant recipients. Our purpose is to describe the design and methods of the MAGIC (Medication Adherence Given Individual SystemCHANGE™) trial

**Methods/Design:**

We report the design of a randomized controlled trial with an attention-control group to test an innovative 6-month SystemCHANGE™ intervention designed to enhance immunosuppressive medication adherence in adult non-adherent kidney transplant recipients from two transplant centers. Grounded in the Socio-Ecological Model, SystemCHANGE™ seeks to systematically improve medication adherence behaviors by identifying and shaping routines, involving supportive others in routines, and using medication taking feedback through small patient-led experiments to change and maintain behavior. After a 3-month screening phase of 190 eligible adult kidney transplant recipients, those who are <85 % adherent as measured by electronic monitoring, will be randomized into a 6-month SystemCHANGE™ intervention or attention-control phase, followed by a 6-month maintenance phase without intervention or attention. Differences in adherence between the two groups will be assessed at baseline, 6 months (intervention phase) and 12 months (maintenance phase). Adherence mediators (social support, systems-thinking) and moderators (ethnicity, perceived health) are examined. Patient outcomes (creatinine/blood urea nitrogen, infection, acute/chronic rejection, graft loss, death) and cost effectiveness are to be examined.

**Discussion:**

Based on the large effect size of 1.4 found in our pilot study, intervention shows great promise for increasing adherence. Grounded in the socio-ecological model, SystemCHANGE™ seeks to systematically improve medication adherence behaviors by identifying and shaping routines, involving supportive others in routines, and using medication taking feedback through small patient-lead experiments to change and maintain behavior. Medication adherence will be measured by electronic monitoring. Medication adherence persistence will be examined by evaluating differences between the two groups at the end of the 6-and 12- month phases. Mediators and moderators of medication adherence will be examined. Patient outcomes will be compared and a cost-effectiveness analysis will be conducted.

**Trial registration:**

ClinicalTrials.gov Registry: NCT02416479 Registered April 3, 2015

## Background

For adults who have a kidney transplant, the leading predictor of rejection, kidney loss, death and their attendant costs is immunosuppressive medications non-adherence [1–5] with an alarming one-third of kidney transplant recipients experiencing this preventable problem [6–8]. According to meta-analysis, predictors of medication nonadherence are nonwhite ethnicity, poorer social support and poorer perceived health [8]. Patients’ most frequent barrier to adhering to immunosuppressive medication is forgetting [9]. Even minor deviations from adherence have shown negative effects, though the precise extent of poor outcomes stemming from nonadherence is not yet clear [10–13]. Traditionally, intervention studies have aimed at boosting adherence target cognition (knowledge, attitudes, beliefs) and behavioral skills. However, these have proven only marginally effective for individuals with acute and chronic illnesses [14–18] and ineffective for adult kidney transplant recipients [19–21]. In a sample of kidney transplant recipients, we test the innovative and successful SystemCHANGE intervention, which is grounded in the Socio-Ecological Model [22–25]. This approach is a paradigm shift in behavioral interventions because it focuses on redesigning the system of the interpersonal environment and daily routines linked to health behavior, rather than focusing on increasing individuals’ motivation and intentions to improve their adherence [22, 26, 27]. Using a four-pronged, patient-centered approach, we: (1) assess individual systems (including important others who shape medication taking), how they influence medication taking and the individual’s proposals for improving medication adherence, (2) implement the proposed individual systems solutions for improving adherence, (3) track adherence data, and (4) evaluate adherence data through small experiments. The effect size of 1.4 found in the SystemCHANGE pilot work was a nearly four-fold greater effect size of most other previous adherence interventions [28].

The effectiveness of interventions to improve medication adherence (MA) in the acute and chronically ill general population has been examined by numerous systematic reviews and meta-analyses [14–16, 29–35]. Typically psychological theories guide interventions to enhance knowledge through education, attitude through counseling, and behavior through skills training. Even with multi-faceted interventions, effect sizes in meta-analyses have been very small. Narrative reviews corroborate findings from meta-analysis that limited benefits occur with interventions focused on motivation and intention. Only about 50 % of studies found statistically significant improvements in MA. Equally disappointing results have been noted in transplant intervention studies which have also focused only on motivation and intention [19–21, 36–40]. Limitations of these studies included: 1) atheoretical approaches, 2) testing interventions that targeted motivation and intentions, 3) a lack of attention to environmental influences on routines and habits, 4) a lack of timely feedback on medication-taking, and 5) no evaluation of intervention cost-effectiveness. This study protocol addresses these limitations.

## Methods

### Aims

The primary aim of the trial is to determine whether the SystemCHANGE™ intervention is more effective than the attention control intervention in improving MA in adult kidney transplant recipients at the completion of the intervention and maintenance phases. We hypothesize adult kidney transplant recipients participating in the SystemCHANGE™ intervention will have higher immunosuppressive MA rates than those participating in the attention control at the completion of intervention and maintenance phases. A secondary aim is to examine the patterns of MA in this group. We will determine when the intervention becomes effective (e.g., what “dose” is needed) and what the pattern of decay in medication adherence is over time in both groups. Our exploratory aims are to determine whether the SystemCHANGE™ intervention is more effective than the attention control in decreasing poor health outcomes (e.g., infection, acute/chronic rejection, graft loss, death, and increasing creatinine/blood urea nitrogen,), to explore potential mediators (social support and systems-thinking) and moderators (ethnicity, perceive health and level of medication nonadherence) of MA, and to determine whether the SystemCHANGE™ intervention is cost-effective. We hypothesize patients in the SystemCHANGE™ intervention will demonstrate lower levels of poor outcomes than attention controls at 12 months. We also hypothesize the cost-effectiveness ratio for the SystemCHANGE™ intervention will be less than the cost-effective ratio for the attention-control intervention.

## Design

This is a 4-year, two-center, randomized controlled trial, that is single-blind (participants [Pps]) and uses a stratified sample block design with repeated measures. We are comparing the SystemCHANGE™ intervention to the attention control intervention in adult kidney transplant recipients with existing medication nonadherence documented by electronic monitoring. The repeated-measures design provides longitudinal data regarding medication nonadherence which allows us to determine when the intervention becomes effective (to determine if a lower dose of SystemCHANGE™, e.g. shorter time of delivery, is possible). It also allows us to track possible decay in medication nonadherence over time following the intervention.

We are examining the experimental effect on the outcome variable MA. During the 3-month screening phase, all Pps are using electronic monitoring to document medication taking. Those who are adherent (MA rate of .85 % or greater) exit the study. To prevent the “ceiling” effect, those with documented medication nonadherence (MA rate of less than .85 %) are stratified by low (<70 %), and moderate (70-84 %) nonadherence, based upon our previous medication nonadherence pattern research [41]. They then enter the intervention phase of the study and are randomized into either the treatment (SystemCHANGE™ intervention) or the attention control group (attention control condition). During the 6-month intervention phase, all Pps receive a home visit at baseline plus six telephone calls (at intervention months 1, 2, 3, 4, 5, 6). In addition, Pps randomized into the SystemCHANGE™ intervention are also guided in implementing SystemCHANGE™ activities related to medication taking by the Research Assistant (RA). Control group Pps receive RA-provided education guided by healthy living patient educational materials. The maintenance phase begins after the intervention and runs for an additional 6 months. This phase examines how Pps maintain MA in the absence of an intervention; however, we are continuing to use electronic monitoring to measure the outcome variable. Health outcome and healthcare cost data are collected during the intervention and maintenance phases.

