Both intervention and attention-control groups use MEMS for 6 months after the 3-month screening phase. This length of time allows adequate time to capture changes in medication-taking behavior [56]. One twice-daily prescribed medication are monitored because previous research has indicated that monitoring a second medication does not provide additional MA information [53]. The monitored immunosuppressive medication is randomly selected by the RA. Random selection of the monitored immunosuppressive medication occurs as follows: The RA numbers all of the twice-daily administered immunosuppressive medications on the Demographics Form. Most Pps will take two immunosuppressive medications twice daily. In this case, the RA will flip a coin to determine which medication will be placed in the MEMS bottle. In the event that the patient has greater than two immunosuppressive medications taken twice daily, the RA will enter the number into a random numbers generator and have the Pp monitor the randomly selected immunosuppressive medication.

Pps are trained on use of the MEMS cap by the RAs. They are instructed to only remove the randomly selected immunosuppressive medication from the MEMS cap and bottle. If a pillbox is used for medications, colored disks/“Tic-Tacs” are placed in the pillbox to remind the Pp to ingest the medication from the MEMS bottle. During the screening phase, at weeks 1 and 8, the RAs telephones the Pp to ask if they are using the MEMS and MEMS diary and if they have any questions about using them. Those Pps who do use a pillbox are asked if they are using the “Tic-Tacs” to remind them to ingest from the MEMS bottle. If there are any deviations from the procedure, the RAs will re-train the Pps.

Beginning the day after the intervention Pps are instructed how to use the cap. Cap openings will be recorded and a cumulative medication taking record generated. This record is sent to the SystemCHANGE™ intervention Pps and reviewed with them at baseline and months 1, 2, 3, 4, 5, and 6. These reports contain a summary report with graphic representation of individual bottle openings and closings within the established time window of +/-1.5 hours, the hours elapsed since the previous opening, missed doses, and drug holidays. The attention-control intervention group will continue to use the MEMS but will not be sent a report since this is the “Study” step of the SystemCHANGE™ intervention.

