Our primary analysis assesses whether the SystemCHANGE™ intervention is more effective than the attention-control intervention in increasing MA in adult kidney transplant recipients at the completion of the 6-month intervention and 6-month maintenance phases. We hypothesize that adult kidney transplant recipients receiving the SystemCHANGE™ intervention will have higher immunosuppressive MA rates than the attention-control group at the completion of intervention and maintenance phases. Since rate responses will most likely violate the normality assumption, the non-parametric method, Mann- Whitney test, will be used for comparing the two groups. However if the normal assumption is satisfied through transformation or as raw data measures, t-test will be applied for group comparison. Possible covariates resulting from demographic data and screening phase MA will be included in the analysis to adjust for possible bias.

Our secondary analysis assesses the MA patterns in both the SystemCHANGE™ and attention-control groups. Specifically we are interested in determining when the intervention becomes effective (e.g., what “dose” is needed) and the pattern of decay in MA over time in both groups. The dependent variable for these research questions are the repeated measurements of immunosuppressive MA rates at 12 time points [i.e. 1, 2, 3, 4, 5, 6, 7, 8, 9, 10, 11 and 12 months] and the independent variable is group assignment and time effect. Poisson regression analysis will be used for these questions. Proc Nlmixed procedure in SAS will be used for Poisson regression modeling. In order to answer the hypothesis we will test for group-by-time interaction to test if the two groups have different time profiles for MA or not. Possible covariates resulting from demographic data and screening phase MA will be included in the model to adjust for possible bias. Repeated measures from the same Pp will be accounted for using a random effect in the model.

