If this SystemCHANGE™ intervention is found to be effective in kidney transplant patients, other chronically ill populations known to have medication nonadherence (those with hypertension, diabetes, TB, asthma, epilepsy) may immediately benefit from this approach while trials are conducted to confirm findings across populations. The obdurate problem of medication nonadherence is rampant. Scientists’ medication nonadherence interventions will move from focusing primarily on interventions to change knowledge, attitudes, and beliefs and instead are focusing on changing the personal environment and shaping daily routines. Clinicians will cease blaming the patient for the inability to adhere to the prescription, but will, within the SystemCHANGE™ framework, support patient-designed, interventionist-guided, small experiments using Deming’s Plan-Do-Check-Act cycle [69] Our pilot study results indicate that the SystemCHANGE™ intervention “dose” may be effective immediately. If these results are supported in this larger study, clinicians could quickly and easily deliver the intervention in the hospital or clinic setting at a reasonable cost. Electronic monitoring systems are constantly improving. Wireless systems are streamlining electronic monitoring of medications, which further enhances the ease of delivery. The findings of this study may also prompt researchers to explore SystemCHANGE™ approaches to changing other important public health problems arising from human behavior (e.g. smoking).

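### The repeated measures can show when the arms separate under 6-month delivery, but not whether a shorter delivery of SystemCHANGE would suffice

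*Protocol article*

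**What the plan says.** **The claim.** The Design section gives a reason for finding the time of onset: "to determine if a lower dose of SystemCHANGE™, e.g. shorter time of delivery, is possible". The secondary aim, in Aims, is worded "We will determine when the intervention becomes effective (e.g., what “dose” is needed", followed by the pattern of decay. Statistical analysis repeats both parts, beginning "Specifically we are interested in determining when the intervention becomes effective", with the same gloss on dose.

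**The delivery.** In Design, "all Pps receive a home visit at baseline plus six telephone calls", the calls being at months 1 to 6. The section on developing the intervention describes monthly evaluation calls and a closing contact after month 6. For electronic-monitor feedback, the primary outcome section says: "This record is sent to the SystemCHANGE™ intervention Pps and reviewed with them at baseline and months 1, 2, 3, 4, 5, and 6". There are two arms, with participants "randomized into either the treatment (SystemCHANGE™ intervention) or the attention control group (attention control condition". The maintenance phase follows the intervention phase and lasts a further six months.

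**The analysis.** Statistical analysis plans a Poisson mixed model on 12 monthly adherence measures, with group and time as independent variables, possible covariates, a random effect for participant and a test of group by time.

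**The Discussion.** It reports that in the pilot the dose may have worked at once and says that, if this trial agrees, "clinicians could quickly and easily deliver the intervention in the hospital or clinic setting at a reasonable cost".

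**The concern.** Whether a shorter programme would do is a question about stopping: what adherence would be if contact ended at month 1, 2 or 3. Time of onset answers a different question, namely when a difference appears while contact is still going on.

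The protocol's own account of the intervention makes the distinction matter. Later calls are active: each reviews the participant's small experiments, and if adherence has not improved the participant is encouraged to try another solution. Controls receive no monitoring reports because that feedback counts as a step of the intervention. The Background also lists the absence of timely feedback among the weaknesses of earlier studies. An effect that depends on continued feedback is therefore a live possibility under the document's own theory, and onset timing cannot tell it apart from an effect that sustains itself after the first contacts. Late separation is equally ambiguous, since it could be a delayed response to early contacts.

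At stake is what may be concluded from the secondary aim. Early separation could be reported as evidence about the dose needed, although the trial holds no information on stopping early.

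**Working it through.** **Plan's own figure.** The dose claim rests on no number. The only related figure is 46 per group, for the 6-month comparison. With a standardised difference of 0.70, two-sided 5% (sidedness is not stated, so assumed) and 90% power, n = 2 × (1.960 + 1.282)² / 0.70² gives 43 per group. The t-test gives 43.9, and dividing by 0.955 for the Mann-Whitney test gives 45.9, so 46. The stated size is consistent with its inputs and has no bearing on this point.

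**What the design varies.**

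| Item | Where stated | Value |
|---|---|---|
| Arms | Design | 2, neither with shorter delivery |
| Delivery durations scheduled for SystemCHANGE | Design; Development of the intervention; Primary outcome | 1 (six months) |
| Participants assigned a shorter duration | follows from the above | 0 of 46 |
| Off-intervention follow-up | Design | months 7 to 12, after six months of delivery only |
| Dose or duration term in the model | Statistical analysis | none |

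Within the SystemCHANGE arm, scheduled cumulative dose at month *k* is fixed by *k*. A group-by-time term therefore describes the between-arm difference along that single schedule. It also tests only whether the profiles differ and does not by itself locate the month of onset, though monthly contrasts could do so.

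**Illustration with assumed values.** Let the between-arm difference at month *k*, when delivery ends at month *L*, be

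D(k; L) = 10 if k ≤ L, and 10 × r^(k − L) if k > L.

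The 10 points is the difference expected at six months in the sample size paragraph. Its presence from month 1 and the monthly retention *r* are assumptions.

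- Truth A: r = 0.95 whether delivery lasts two or six months.
- Truth B: r = 0.95 after six months of delivery, but r = 0.50 after two months.

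Under six-month delivery, the only schedule in the trial, A and B give the same curve: 10 points in months 1 to 6, then 10 × 0.95⁶ = 7.4 at month 12.

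Under two-month delivery, which nobody is assigned:

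| | Month 6 | Month 12 |
|---|---|---|
| Truth A | 10 × 0.95⁴ = 8.1 | 10 × 0.95¹⁰ = 6.0 |
| Truth B | 10 × 0.50⁴ = 0.6 | 10 × 0.50¹⁰ = 0.0 |

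More generally, retention after two months could lie anywhere from 0 to 1, giving 0 to 10 points at month 6, without changing anything this trial observes. An onset measured without error at month 1 would not narrow that range.

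**The case against.** Most of the targeted text is answerable. Twelve monthly measures in two randomised arms can address when the arms separate and how adherence decays after month 6. A reader might infer that the whole secondary aim fails; it does not. Only the step from onset to dose is unsupported.

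The dose language sits in parentheses, and the Design section asks whether a lower dose is possible, not whether it is equivalent. A reader might infer a planned rule that turns early separation into shorter delivery. No such rule, dose model or threshold is described; the plan goes no further than a group-by-time test. Even so, the text says the design lets the team determine the matter, and nowhere labels it hypothesis-generating.

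A reader might also take the Discussion to recommend cutting the programme to a single visit. It does not mention one visit or ending the monthly calls. The sentence concerns setting, ease and cost, and it is conditional. What remains is an uncaveated move from an immediate effect to quick delivery.

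Finally, received dose may vary. The Treatment fidelity section records the number, length and spacing of sessions, so dose and time coincide in the schedule but not necessarily in delivery. That variation is not randomised and no analysis of it is described, so it does not rescue the claim.

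That the aim is secondary and the remedy is wording is correct, and it limits the weight of the point.

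**Conclusion.** The point holds for the lower-dose claim in Design and for the gloss equating onset with dose in Aims and Statistical analysis. The trial can estimate time to separation under continuing delivery and decay after six months of delivery. It cannot estimate whether the effect would persist had delivery stopped earlier.

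The size is categorical: one scheduled duration, none of 46 assigned a shorter one, and hence no identification at any sample size. The 8.1 and 0.6 points only illustrate this and depend on assumed retention; the conclusion does not. It rests on the article describing the schedule completely, with no shorter arm, second randomisation or planned early stop. An analysis plan not shown could not supply randomised durations. The 6- and 12-month primary comparison, its error rate and its power are untouched.

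**What to change.** - **Design:** delete the parenthetical lower-dose claim, or replace it with a statement that the repeated measures describe onset under continuous 6-month delivery and decay afterwards.
- **Aims and Statistical analysis:** drop the dose gloss. State the secondary aim as time to a between-group difference under continuous 6-month delivery, and decay after it.
- **In the same places:** say that early onset would only generate a hypothesis for a later trial that randomises delivery duration.
- **Discussion:** attach the same caveat to the step from an immediate effect to quick delivery.

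The cost is wording only. Arms, contacts, sample size, data and primary analysis stay as they are, and the stated reach of the secondary aim becomes narrower.
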